#### Statistical analysis plan

3.6.2

Details on statistical analyses are specified in the statistical analysis plan (SAP) prepared and finalized before the analysis, although the basic policy is to compare groups for the items described below. The significance level in testing the primary non‐inferiority hypothesis is one‐sided .05 and that for all other secondary endpoints is one‐sided .05.

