## OBJECTIVES

2

The primary objective of the present study is to demonstrate the non‐inferiority of escitalopram to duloxetine in acceptability (treatment discontinuation rate) at week 52 in an RCT for patients with non‐psychotic MDD, as defined by the Diagnostic and Statistical Manual of Mental Disorders, Fourth Edition (DSM‐IV), who were identified as suboptimal responders exhibiting symptoms of at least moderate severity (scoring at least four points on the Clinical Global Impression of Severity score (CGI‐S^39^) after at least 3 weeks of treatment with second‐generation antidepressants other than escitalopram and duloxetine at a therapeutic dose.

The secondary objectives of this study are as follows: (a) to compare acceptability (treatment discontinuation rate) at week 8 and week 16 between the allocated treatment, (b) to compare acceptability (treatment discontinuation rate) during week 16 and 52 between the allocated treatment, (c) to compare the proportion of cases who terminate the trial due to the achievement of remission for more than 6 months, (d) to compare efficacy at week 8, week 16, and week 52 between the allocated treatment in terms of severity, responses, and remission rates, and (e) to compare health outcomes at week 8, week 16, and week 52 between the allocated treatment. We will also investigate the incidence of adverse events in order to evaluate safety.

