##### Analyses for secondary outcomes

Regarding repeated measurements of continuous endpoints in Step 1, a mixed‐effects model for repeated measurements (MMRM) with an unstructured covariance matrix will be used to compare mean changes from the baseline between two groups. Degrees of freedom for errors will be adjusted with the Kenward‐Roger method. The 95% CI for the proportion in each binary endpoint will be estimated using the Clopper‐Pearson method, and proportions will be compared with the chi‐squared test. In analyses of Step 2 data, the proportion of patients who switched the study medication will be summarized, and data will be summarized for the randomized group and for each pattern of the switched treatment.

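### Secondary endpoints are assigned a one-sided .05 level, but their objectives and named tests have no direction

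*Protocol article*

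**What the plan says.** Section 3.6.2 gives the two levels in one sentence. For the primary analysis: "The significance level in testing the primary non‐inferiority hypothesis is one‐sided .05". For the rest: "that for all other secondary endpoints is one‐sided .05".

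Section 2 (Objectives) lists five secondary objectives, all worded as comparisons. For example:
- discontinuation: "to compare acceptability (treatment discontinuation rate) at week 8 and week 16 between the allocated treatment"
- efficacy: "to compare efficacy at week 8, week 16, and week 52 between the allocated treatment in terms of severity, responses, and remission rates"
- health outcomes: "to compare health outcomes at week 8, week 16, and week 52 between the allocated treatment"

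Section 3.6.4 (Analyses for secondary outcomes) names the methods. For repeated continuous measures in Step 1, an MMRM "will be used to compare mean changes from the baseline between two groups". For binary endpoints, "proportions will be compared with the chi‐squared test".

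The only test given a direction and a margin is the primary one in section 3.6.3: escitalopram minus duloxetine in week 52 discontinuation, with an upper confidence limit to be below 10%.

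**The concern.** A one-sided level needs a stated alternative: which arm is expected to do better, or which arm must not be worse and by how much. The primary endpoint has this. No secondary endpoint does.

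The Background does not supply a direction either. It cites evidence that SNRIs are more efficacious than SSRIs as a class. It also cites head-to-head evidence leaning towards escitalopram over duloxetine (OR 1.30, 95% CI 0.88 to 1.91). A secondary result in either direction would be of interest.

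At stake is which secondary differences are called significant. Read one way, the rule is more lenient than a reader would assume for a two-group comparison. Read the other way, it excludes findings in a direction that the protocol never identifies.

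**Working it through.** The protocol gives no power or sample size figure for the secondary endpoints, so there is no stated figure to reproduce. The check asks what the stated level implies for the stated tests.

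**Inputs.** Level: one-sided .05 (3.6.2). Tests: chi-squared for proportions and MMRM for mean changes (3.6.4). Group size: 121 (3.6.1). Event rates of .3 and .5 are assumptions for illustration.

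**Step 1: critical values.**
- One-sided .05: z = 1.645. For a comparison of two proportions the 1-df chi-squared statistic is z squared, so the cut-off is 2.706.
- Two-sided .05: z = 1.960, so the chi-squared cut-off is 3.841.

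**Step 2: error rate under each reading of the rule.**
- Either direction may be claimed at |z| > 1.645: error = 2 × (1 − Φ(1.645)) = 2 × .05 = .10.
- Only one direction, fixed in advance, may be claimed: error = .05, and a difference of any size the other way cannot be declared.
- Two-sided .05: error = 2 × (1 − Φ(1.960)) = .05, with both directions open.

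**Step 3: exact check for the chi-squared test.** Exact binomial enumeration of the Pearson test with 121 per group and no true difference, counting rejections in both directions:

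| Common rate | Cut-off 2.706 | Cut-off 3.841 |
|---|---|---|
| .3 | .102 | .050 |
| .5 | .108 | .046 |

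The normal approximation in step 2 is adequate at this sample size.

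**Step 4: smallest significant difference.** With rates near 50% and 121 per group, SE = √(.5 × .5 × 2 / 121) = √(.5 / 121) = .0643.
- 1.645 × .0643 = .106, or 10.6 percentage points.
- 1.960 × .0643 = .126, or 12.6 percentage points.

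Under the either-direction reading, an observed difference between 10.6 and 12.6 points would be called significant although it misses two-sided .05.

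**Step 5: which reading does the text support?** Section 2 gives no direction for any of the five secondary objectives. Section 3.6.4 gives none for either method, and the chi-squared statistic discards the sign of the difference. The MMRM contrast does carry a sign and could be tested one-sided, but the protocol does not say towards which arm. The text does not decide between the first two readings in step 2.

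**The case against.** The strongest reply is that a one-sided .05 test has a 5% error rate by construction. The signed root of a 1-df chi-squared statistic gives a valid one-sided test, and MMRM contrasts can be tested one-sided. Section 3.6.2 also refers to an SAP finalised before analysis, which could name the directions. The trial hypothesis at the end of the Background, that escitalopram is at least as acceptable as duloxetine, might be meant to carry over to the secondary discontinuation endpoints.

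Part of this stands. The 10% rate is conditional on claims being allowed either way, and the unseen SAP may settle the matter. But the protocol itself fixes the level, so this is a stated rule that does not fit, not a detail deferred. The acceptability hypothesis gives no margin for any secondary endpoint and says nothing about the direction for quality of life or functioning.

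Three stronger readings are tempting and are not supported:
- A reader might infer that the 95% intervals in 3.6.4 clash with the test level. They do not: "The 95% CI for the proportion in each binary endpoint will be estimated using the Clopper‐Pearson method" describes an interval for a single proportion, not for the between-group difference.
- A reader might infer that the error rate simply doubles for every secondary test. It does so only where either direction may be claimed.
- A reader might compound the error over many endpoints as if they were independent. Response and remission both derive from the PHQ-9, which also measures severity, and the same patients are compared at several time points, so the endpoints are correlated. Multiplicity is also a separate question, which changing the sidedness would not resolve.

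**Conclusion.** The concern holds in a limited form. The secondary level is one-sided while the secondary objectives and named analyses have no direction. The consequence is one of two things, and the protocol does not say which. Either the per-test error is 10% rather than 5%, or an unnamed direction is closed to any finding.

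The 10% figure assumes that significance may be claimed in either direction. The values 10.6 and 12.6 points assume 121 per group and rates near 50%. For the MMRM contrasts, the normal critical values approximate the corresponding t values.

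The consequence is confined to secondary claims. The primary non-inferiority test, which has both a direction and a margin, is untouched.

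**What to change.** In section 3.6.2, replace the secondary half of the sentence with: secondary endpoints are tested at a two-sided significance level of .05, with two-sided 95% confidence intervals for the between-group differences. Leave the primary level as it is. If the SAP already says this, bring the protocol sentence into line with it.

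If one-sided secondary tests are really intended, the inconsistency could instead be removed by naming the direction of each one and specifying a directional test. That takes more text and gives up findings in the other direction.

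The cost of the recommended change is one sentence and a slightly stricter threshold: the critical value in any given direction moves from 1.645 to 1.960. No extra data or patients are needed. The wording should be settled before the secondary results are analysed.

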#### Primary analyses

3.6.3

The primary analysis population in this study is ITT (intention to treat). All patients enrolled in this study need to be included in the analysis, except those who did not take the study medication.

Acceptability—Our primary endpoint is attrition and withdrawal rates from the allocated treatment for any reason at week 52. The non‐inferiority of escitalopram to duloxetine will be tested using the one‐sided 95% CI for the between‐group difference in the discontinuation rate (escitalopram − duloxetine). The CI is estimated with the normal approximation. If the upper limit of the one‐sided 95% CI is less than the non‐inferiority margin (Δ = 10%), escitalopram is considered to be non‐inferior to duloxetine in the primary endpoint.

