**Methods:**

This is a two‐arm, three‐phased randomized controlled trial in which independent assessors will be blinded while treating psychiatrists and patients remain unblinded to treatment allocation. Patients will be randomized to escitalopram or duloxetine in Step 1 (8 weeks), and when entering Step 2 (8 weeks), the drug will be switched to the other if the first one is not effective at the end of Step 1. The acceptability of the allocated drugs, improvements in depression from baseline, adverse events, and attrition rates will be recorded and assessed for up to 52 weeks, including the follow‐up step.

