Randomization will be conducted using the central computerized registration system and the subject will be allocated to receive one of the study medications (escitalopram or duloxetine), which is conveyed to the treating psychiatrist by a clinical research coordinator, and will be tapered from their current antidepressant (switched by the cross‐titration and tapering method) by week 4 in the Step 1 treatment. Treatment allocation is blinded to central raters throughout this study.

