#### Step 2 treatment and naturalistic follow‐up

3.4.3

The protocol strongly encourages patients to continue Step 1 medication if patients do not meet the switching criteria and to alter Step 1 medication if they do. They receive another 8‐week treatment using a flexible‐dose schedule to maximize the chance of remission, except for those with clear intolerance or significant clinical worsening based on CGI‐I score ≥ 6 at two consecutive visits. The recommended schedule is bi‐weekly appointments as well as the Step 1 treatment, and optional visits are allowed in accordance with clinical needs.

After week 16, all patients will be followed up to week 52 in order to assess adherence, efficacy, adverse events, and natural courses. There will be no prohibited treatment during the follow‐up, and patients will be encouraged to visit every 4 weeks even if antidepressants are discontinued.

#### Discontinuation during Step 1 and Step 2

3.4.4

Discontinuation from the allocated treatment (in Step 1 and Step 2) will be decided as follows:
The treating psychiatrist's judgment that disadvantages from adverse effects outweigh benefits from continuing the allocated treatment.Patient wishes for withdrawal from the allocated drug.Significant clinical worsening based on CGI‐I score ≥ 6 (ie, much worse or very much worse) at two consecutive visits.Urgent risk of suicide, self‐injury, or harming others.Getting pregnant.Occurrence of severe or unstable comorbidities including cardiovascular, hepatic, renal, respiratory, hematological, endocrinal, and neurological diseases.Occurrence of a clinically significant abnormality in ECG (QTc > 450 ms in men, >470 ms in women).Clinical judgment by the treating psychiatrist that the continuation of the allocated treatment is not possible, inappropriate, or unsuitable for other reasons.Observation of major protocol deviations.

When the allocated treatment is halted, the treating psychiatrist will explain this to the subject. In the case of adverse effects, appropriate observations, examinations, and procedures are implemented by the treating psychiatrist. Following the discontinuation of the allocated treatment in Step 1 and Step 2, patients are still followed up until week 52 unless they withdraw their consent. Similarly, even in the case of major protocol deviations, patients will be followed up until week 52, except for the withdrawal of consent by the subject or discontinuation decided by the treating psychiatrists.

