#### Primary outcome measures

3.5.1

The primary endpoint of the present study is the rate of discontinuation for any reason at week 52. The discontinuation of study medication will be further divided into seven subgroups based on the reason for discontinuation ascertained by the treating psychiatrist at the time of the subject's discontinuation and will be confirmed by the Data Safety Monitoring Committee (DSMC).
Discontinuation due to intolerance is deemed by the treating psychiatrist while its validity needs to be evaluated by the scores of FIBSER^46^ (Frequency, Intensity, and Burden of Side Effects Rating) and EQ5D.Discontinuation due to the lack of efficacy is applied when initiated by patients or their related persons claiming that the allocated drug is not effective and they want to stop using it.Discontinuation due to significant deterioration is defined as CGI‐I score ≥ 6 (worse or markedly worse) in two consecutive visits. Treating psychiatrists must stop using the allocated drug.Discontinuation due to consent withdrawal is applied when a written withdrawal form is submitted by the subject. Reasons for withdrawal will be further analyzed and may be reclassified to other reasons for discontinuation.Discontinuation due to other safety issues, such as gestation, accidents, or admission to hospital with a physical illness, is deemed by the treating psychiatrist or patients.Discontinuation due to a loss to the follow‐up for inevitable reasons such as moving.Discontinuation due to other reasons.

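### The primary population is called ITT but drops patients who never took study medication, an exclusion that can depend on the arm in this unblinded trial and can remove primary-endpoint events

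*Protocol article*

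**What the plan says.** Section 3.6.3 (Primary analyses) makes two statements in succession. The first is "The primary analysis population in this study is ITT (intention to treat". The second is "All patients enrolled in this study need to be included in the analysis, except those who did not take the study medication". The same section defines the outcome: "Our primary endpoint is attrition and withdrawal rates from the allocated treatment for any reason at week 52". Non-inferiority is declared if the upper limit of the one-sided 95% CI for escitalopram minus duloxetine, by the normal approximation, lies below 10 points.

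On blinding, the Abstract (Methods) says that "treating psychiatrists and patients remain unblinded to treatment allocation"; only the central raters are blinded. Section 3.2 places randomisation after baseline. The allocation, "which is conveyed to the treating psychiatrist by a clinical research coordinator", comes before the cross-titration from the current antidepressant.

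Section 3.5.1 lists consent withdrawal among the seven kinds of discontinuation: "Discontinuation due to consent withdrawal is applied when a written withdrawal form is submitted by the subject". Section 3.4.4 lists as a ground for stopping: "Patient wishes for withdrawal from the allocated drug". It also says that after stopping, "patients are still followed up until week 52 unless they withdraw their consent".

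The article nowhere says that a patient who never starts is counted as a discontinuation, and it names no analysis of all randomised patients.

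**The concern.** A set that removes patients for something that happens after randomisation is not an intention-to-treat set, whatever it is called. Dropping never-dosed patients is usually defended on the ground that, under blinding, the decision not to start cannot depend on the arm. That defence is not available here, because prescriber and patient both know the drug before the first dose. Patients also enter already taking another antidepressant, so declining the assigned one is a practical option.

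The outcome makes this more than a labelling matter. The trial measures acceptability as all-cause withdrawal from the allocated treatment. A patient who declines the drug on learning the allocation has not accepted it, yet the stated rule takes that patient out of both numerator and denominator. If the share who never start differs by arm, the primary difference shifts and the non-inferiority test no longer has its nominal error rate.

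**Working it through.** **Plan's own figure.** The protocol gives none on this point: no never-starter rate, count or allowance. The derivation of the 242 is a separate matter and is not needed here.

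**Inputs from the protocol.** 121 per group, margin 10 points and one-sided alpha .05 (sections 3.6.1 and 3.6.3); escitalopram attrition 49% and an expected difference of 8 points (section 3.6.1), read as duloxetine 57%.

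**Assumptions.** The shares who never start, u_E on escitalopram and u_D on duloxetine, are assumed and varied in both directions. Every never-starter counts as an event in the all-randomised rate p. For the error rate at the margin, the true all-randomised rates are set at 59% v 49%.

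**Formulas.** The rate among takers is q = (p − u)/(1 − u). The number analysed per arm is n = 121(1 − u). The standard error is SE = √[q_E(1 − q_E)/n_E + q_D(1 − q_D)/n_D]. The chance of declaring non-inferiority is Φ{[0.10 − (q_E − q_D)]/SE − 1.645}.

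**One case in full (6% v 1%).** q_E = (.59 − .06)/.94 = .564 and q_D = (.49 − .01)/.99 = .485, a difference of 7.9 points. With n = 113.7 and 119.8, SE = .0652. Then (.100 − .079)/.0652 − 1.645 = −1.32, and Φ(−1.32) = 9.3%.

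| Never start, escitalopram v duloxetine | Takers-only difference (points) | Chance of false non-inferiority |
|---|---|---|
| none excluded | +10.0 | 5.0% |
| 6% v 1% | +7.9 | 9.3% |
| 4% v 1% | +8.8 | 7.2% |
| 2% v 1% | +9.7 | 5.5% |
| 1% v 1% | +10.1 | 4.8% |
| 5% v 5% | +10.5 | 4.2% |
| 1% v 4% | +11.7 | 2.8% |
| 1% v 6% | +12.8 | 1.9% |

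**Other true rates.** With 67% v 57%, also at the margin, the pattern is the same: 5% v 0% gives 8.5% and 0% v 5% gives 2.3%. At the planning rates of 49% v 57%, the chance of declaring non-inferiority is 87.9% with everyone analysed, 94.0% with 5% v 0% excluded and 78.2% with 0% v 5% excluded.

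**How few patients it takes in a borderline trial.**
- With 69/121 v 69/121 the difference is 0 and the upper limit is 1.645 × .0636 = 10.5%, which fails. Drop 3 never-starters on escitalopram and 1 on duloxetine: 66/118 v 68/120 gives −0.7 + 1.645 × 6.43 = 9.8%, which passes.
- In the other direction, 68/121 v 69/121 gives −0.8 + 1.645 × 6.37 = 9.7%, which passes. Drop 1 on escitalopram and 3 on duloxetine: 67/120 v 66/118 gives −0.1 + 1.645 × 6.44 = 10.5%, which fails.

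**Effect of the fix when shares are equal.** If both arms have share u, the all-randomised difference is (1 − u) times the takers' difference. At 5% v 5% that is .95 × 10.5 = 10.0, a slight pull toward zero.

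**The case against.** A reader might infer that the exclusion favours escitalopram and nearly doubles the false-positive rate. The documents do not support that. They give no never-starter rate and no direction. What they do report on dropout (section 1: odds ratio 0.52, 95% CI 0.26 to 1.01, lower on escitalopram) concerns stopping rather than refusing to start, and gives no reason to expect more refusals on escitalopram. With equal shares, or more refusals on duloxetine, the planned exclusion is conservative.

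Never-starters may also be few. Full explanation and written consent come before randomisation. The psychiatrist must judge the study medication appropriate. Failure of either drug at maximum dose in the previous episode is an exclusion.

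Nor is every never-starter reacting to the allocation: some may move away or fall ill. This limits how strongly such patients can be called non-acceptors, but matters less than it seems, since the endpoint counts any reason.

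It can also be said that discontinuing a medication presupposes starting it, so a treated-only question is coherent. It is, but it is not ITT, and in an unblinded trial it is the less protected comparison. The SAP, which is not shown, may contain an all-randomised sensitivity analysis. That would not cure the primary definition stated in section 3.6.3.

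What stands of the objection is that size and direction are unknown, and that the wording alone does not show the primary result to be invalid.

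**Conclusion.** The defect holds as a matter of text and design. The primary set is labelled ITT but is not, the exclusion comes after an allocation known to patient and prescriber, and it can remove events of the primary endpoint. The word enrolled in place of randomised does not change this, because the rule as written still covers randomised patients who never start.

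The consequence can be given only as a range under assumed shares. With true rates at the margin (59% v 49%) and between 1% and 6% never starting per arm, the chance of false non-inferiority runs from 1.9% to 9.3% against a nominal 5%. It is 4.8% at 1% v 1%, so the effect is negligible if nearly everyone starts. Confidence is high in the contradiction and in the better rule, and low in any particular size or direction of bias.

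**What to change.** In section 3.6.3, and in the SAP to match:
- Make all randomised patients, analysed by randomised arm, the primary population, and count never starting the assigned drug as discontinuation.
- Keep the treated-only set under its own name, as a sensitivity analysis and for safety.
- Report the number of never-starters by arm, with reasons where recorded.
- Show both sets beside the non-inferiority conclusion, because counting equal shares of never-starters as events pulls the difference slightly toward zero.

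The cost is a few sentences. The planned 242 is unchanged, and a never-starter's outcome under this rule is known without new data. Event rates rise slightly in both arms. The article reports the study as accomplished in March 2018, so the change now falls on analysis and reporting, and is feasible if records of never-starters were kept. If the analysis has already been run, the minimum is to correct the ITT label, give the counts by arm and present the all-randomised result alongside.

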### Recruitment, screening, and baseline assessment

3.2

Recruitment is processed at participating clinical sites, which consist of two university hospitals (Keio and Showa Universities) located in central Tokyo along with their branch hospitals and clinics, and the National Center of Neurology and Psychiatry (NCNP) located in the outskirts of Tokyo, Japan.

Potential patients are referred by their treating psychiatrists, who provide brief information, during ordinal appointments, about the study using a brochure. When patients express interest in participation, a research team arranges an appointment with the patient for a detailed explanation. Not only the study design, but also its potential benefits and risks are thoroughly disclosed. Informed consent with written documents will be obtained by the investigator or a person designated by the investigator when the patient agrees to participate in the study. Patients will be screened by a treating psychiatrist in order to establish whether they meet the inclusion and exclusion criteria (described below). The M.I.N.I.^40^ (Mini‐International Neuropsychiatric Interview) will be used to confirm the MDD diagnosis and also comorbid Axis I diagnosis in order to exclude cases if other primary psychiatric disorders exist. The severity of depression will also be evaluated by PHQ‐9 41 (Patients Health Questionnaire‐9 items) and CGI‐S 39 by their treating psychiatrist. Every treating psychiatrist has been trained in the administration of semi‐structured interviews.

Demographic and clinical characteristics, including the duration of the depressive episode, will be assessed. Furthermore, an electrocardiogram (ECG) will be performed to rule out extreme QTc prolongation defined in the exclusion criteria. Standard ECG or alternative portable ECG (READ MY HEART Plus®) (http://www.jhf.or.jp/ecg/type.html) will be used to evaluate QTc. Blood drawing will also be conducted.

Baseline assessments will be scheduled within no longer than 2 weeks from screening for those who meet inclusion and exclusion criteria. At the baseline, the severity of depression will be assessed by QIDS‐SR_16_
42 (16 items Quick Inventory of Depressive Symptomatology—Self‐Reported) and CGI‐S. Quality of life will be assessed by EQ‐5D^43^ (European Quality of Life Questionnaire‐5 Dimension). Central raters will evaluate depression severity by PHQ‐9 and the level of functional impairment by the Sheehan Disability Scale (SDS)^44^ via telephone.

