#### Sample size calculation

3.6.1

The sample size needed will be 242 (n = 121 per group) in order to demonstrate the non‐inferiority of escitalopram to duloxetine with respect to the proportion of patients who discontinue the study at week 52. The sample size is based on the findings of the MANGA meta‐analysis,^35^ which estimated the between‐group difference in the attrition rate at week 52 to be 8%, and the attrition rate of escitalopram at week 52 was inferred to be 49% according to a previous study.^20^ Using a non‐inferiority margin of 10%, 242 patients need to be enrolled in order to achieve a statistical power of .8 with one‐sided alpha = .05.^35^

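### The primary risk difference and the binary secondary comparisons are planned without baseline covariates that the trial collects, which is valid but probably gives up a little precision

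*Protocol article*

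**What the plan says.** Section 3.6.3 (Primary analyses) takes the difference in discontinuation rates at week 52, escitalopram minus duloxetine. On the interval it says "The CI is estimated with the normal approximation". The decision rule begins "If the upper limit of the one‐sided 95% CI is less than the non‐inferiority margin (Δ = 10" (per cent), and escitalopram is then declared non-inferior. No covariate or stratum is named. All enrolled patients are analysed except those who took no study medication.

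Section 3.6.4 (Analyses for secondary outcomes) gives Clopper-Pearson intervals for each binary endpoint, "and proportions will be compared with the" chi-squared test. Section 3.5.2 makes response and remission binary endpoints on the PHQ-9 and defines response against the baseline PHQ-9 score.

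Section 3.2 lists what is known at entry. The sentence "At the baseline, the severity of depression will be assessed by" goes on to name QIDS-SR16 and CGI-S. EQ-5D is also recorded, central raters score PHQ-9 and SDS by telephone, and demographic and clinical characteristics include episode duration.

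Section 3.6.2 leaves detail to a separate statistical analysis plan, which is not available here, and calls what follows the basic policy.

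**The concern.** Where baseline variables predict a binary outcome, a randomised comparison that uses them estimates the same marginal risk difference with a smaller standard error. Here the upper limit of a single interval is compared with a fixed 10-point margin, so a shorter interval raises the chance of correctly concluding non-inferiority without enrolling more patients. The covariates are already being collected, and the method stated for the primary test does not use them. The same holds for response and remission, where baseline PHQ-9 is an obvious covariate.

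What is at stake is efficiency. The type I error and the meaning of the estimate are not in question.

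**Working it through.** **Inputs from section 3.6.1.**
- Escitalopram rate: "the attrition rate of escitalopram at week 52 was inferred to be 49" per cent.
- Assumed difference: "difference in the attrition rate at week 52 to be 8" per cent. I read this as favouring escitalopram, so duloxetine is 57%. The opposite direction (duloxetine 41%) would need about 7,600 per arm.
- Margin and size: "margin of 10%, 242 patients need to be enrolled", which is 121 per arm.
- Error rates: "a statistical power of .8 with one‐sided alpha = .05".

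**Assumption.** R² is the share of outcome variance explained by baseline covariates. The article gives no value, so a range is shown.

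**The plan's own sample size.** The distance from the assumed difference to the margin is 0.10 + 0.08 = 0.18. The unpooled formula is n = [0.49×0.51 + 0.57×0.43] × (z₁₋α + z₀.₈₀)² / 0.18².
- At one-sided .05: 0.4950 × (1.645 + 0.842)² / 0.0324 = 94.5, so 95 per arm (190 in total).
- At one-sided .025: 120 per arm. With a pooled variance it is 120.7, so 121.

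The stated 242 therefore matches one-sided .025 and does not follow from the stated .05. That is a separate matter. The rest uses 121 per arm and the stated .05.

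**Unadjusted precision and power.**
- SE = √[(0.2499 + 0.2451)/121] = 0.0640, or 6.40 points.
- Distance from estimate to upper limit = 1.645 × 6.40 = 10.5 points.
- Power = Φ(0.18/0.0640 − 1.645) = 87.9%.

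**With adjustment.** The SE is multiplied by √(1 − R²). The equivalent unadjusted size is 121/(1 − R²).

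| Assumed R² | SE (points) | Distance to upper limit (points) | Power, one-sided .05 | Equivalent n per arm |
|---|---|---|---|---|
| 0 | 6.40 | 10.5 | 87.9% | 121 |
| 2% | 6.33 | 10.4 | 88.5% | 123.5 |
| 5% | 6.23 | 10.3 | 89.3% | 127.4 |
| 10% | 6.07 | 10.0 | 90.7% | 134.4 |

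Over R² of 2% to 10%, the gain is 0.1 to 0.5 points of interval and 0.6 to 2.8 points of power.

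**Check of the approximation.** Logistic regression with standardisation was simulated at 121 per arm (1,500 trials per setting, one normally distributed covariate). The ratio of adjusted to unadjusted standard deviation was 1.002 at R² = 0, 0.987 at 2.1%, 0.965 at 5.5% and 0.939 at 11.1%. The corresponding values of √(1 − R²) are 1, 0.989, 0.972 and 0.943. A useless covariate cost almost nothing. The mean adjusted and unadjusted estimates agreed to within 0.1 point.

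**If the assumed advantage is smaller.**
- With a true benefit of 5 points (49% v 54%), the SE is 6.42 points. Power is Φ(0.15/0.0642 − 1.645) = 75.6% unadjusted, and 79.4% at R² of 10%.
- With both rates at 49%, power is 46.5% unadjusted and 49.8% at R² of 10%.

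**The case against.** The strongest reply is that nothing here is wrong. A raw risk difference is a valid estimate under randomisation, and it is on the scale used for the margin and the sample size. At the stated inputs its power exceeds the 80% target. Covariate lists and adjusted sensitivity analyses may also stand in the statistical analysis plan. All of this is correct. It leaves an efficiency point about a method that section 3.6.3 does state.

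Four further objections stand and limit the point.
- **The gain is not shown.** A reader might infer that the interval is certainly wider than it need be. The article does not support this, because it nowhere reports how well any baseline variable predicts discontinuation. The endpoint in section 3.5.1 mixes intolerance, lack of efficacy, withdrawal of consent, accidents and moving away. CGI-S is restricted to 4 or more at entry. The gain may be nil.
- **Prior treatment.** A reader might count the failed first drug among the collected covariates. Section 3.2 does not list it. It is only implied by the eligibility criteria.
- **Chance imbalance.** Removing it is not a second benefit. The unadjusted interval already allows for it, and removing it is the same precision gain.
- **Cost.** Adjustment is not entirely free. A missing baseline PHQ-9 could drop a patient whom section 3.6.3 requires in the analysis. The article also reports completion in March 2018 and was published in September 2019, so replacing the primary estimator of an open-label trial could look post hoc.

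The last two practical costs can be met with an imputation rule and a condition on timing.

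**Conclusion.** The point holds as an optional improvement of low severity. The primary and binary secondary comparisons are stated as unadjusted although suitable baseline data are collected, and this probably gives up some precision. For R² of 2% to 10%, the loss is 0.6 to 2.8 points of power at the planned rates, or roughly 2 to 13 patients per arm. At R² of 0 there is no loss. These figures rest on rates of 49% and 57%, 121 per arm, one-sided .05 and an assumed R².

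Two stronger readings are not supported. One is that the planned analysis is biased or invalid; randomisation protects it. The other is that adjustment would secure the trial's power if the 8-point advantage is wrong. With equal rates, power stays near 50% even at R² of 10%, so that assumption matters far more than the choice of estimator.

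**What to change.** Before any unblinded analysis, prespecify the following.
- **Primary estimate:** the week-52 risk difference by standardisation (g-computation) from a logistic model with treatment and a short list of collected covariates, for example baseline PHQ-9, CGI-S and age. Use a robust or delta-method standard error, and compare the one-sided 95% upper limit with the same 10-point margin.
- **Missing baseline values:** a simple rule, such as single imputation, so that no patient is dropped.
- **Sensitivity analysis:** the unadjusted difference with its normal-approximation interval.
- **Response and remission:** models adjusted for baseline PHQ-9 in place of the plain chi-squared test.

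If outcomes by arm have already been seen, keep the published unadjusted test as primary and label the adjusted analysis supplementary. The cost is wording in the statistical analysis plan and a few lines of code. No new data or patients are needed, and the margin does not change.
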